#### Randomization

2.6.2

According to the enrollment order, eligible participants will be randomly assigned in a 1:1 ratio to either the EA or the sham EA group. An independent statistician will generate the randomization sequence using SPSS software (version 26.0; IBM Corp., Armonk, NY, USA), employing a simple randomization procedure. The allocation sequence will be concealed using sequentially numbered, opaque, sealed envelopes (SNOSE) until baseline assessments are completed and the participant is assigned to a treatment group (27, 28).

#### Blinding

2.6.3

This study is designed as a randomized, single-blind trial. Participants, outcome assessors, and data analysts will remain blinded throughout the trial. Due to the nature of the interventions, the acupuncturists administering the treatment cannot be blinded. To maintain blinding integrity, all research staff (except for the acupuncturists) will receive standardized training to prevent unintentional unblinding. The same assigned acupuncturist will administer all treatment sessions for a given participant to ensure consistency. After baseline data collection, the assigned acupuncturist will open the envelope to reveal the group-specific instructions. Based on the group assignment, real electroacupuncture and sham electroacupuncture procedures will be performed in separate consultation rooms. A dedicated appointment scheduling system will ensure that participants from different groups are treated at various times and do not encounter each other. This measure is implemented to prevent communication between participants from different groups, thereby safeguarding the blinding of participants and the validity of the study outcomes. The success of participant blinding will be assessed upon completion of the entire treatment period (before outcome assessment). Participants will be asked: “Which treatment do you believe you received?” with the following response options: (a) real electroacupuncture, (b) sham electroacupuncture, (c) unsure, or (d) do not care. The integrity of blinding will be quantitatively evaluated using Bang's blinding index (29).

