### Operator qualifications and standardization

2.3

Two licensed acupuncturists will perform all acupuncture procedures, each with at least five years of clinical experience and a nationally recognized acupuncture practice certificate. Before the study commencement, all operators will undergo a one-week standardized training program covering acupoint localization, needle insertion depth, manipulation techniques, and safety protocols. Inter-operator consistency will be assessed through simulated treatment sessions, requiring at least 85% agreement on key parameters (e.g., acupoint localization accuracy, insertion depth, and manipulation frequency).

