### Interventions

2.4

Before treatment, participants will be instructed to empty their bladders and assume a supine position. All treatments will be administered following skin disinfection. Disposable sterile acupuncture needles (Guizhou Andi Pharmaceutical Equipment Co., Ltd.; sizes: 0.30 mm × 75 mm and 0.30 mm × 25 mm) will be used. Participants will receive three weekly treatment sessions (on alternate days), 30 min per treatment session, totaling 18 sessions over 6 weeks.

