To bridge this critical gap, namely, the lack of a systematic evaluation integrating subjective symptoms with objective physiological and structural measures, we designed this randomized, single-blind, sham-controlled trial in accordance with the SHARE guidelines (20) to rigorously assess the specific effects of EA. By employing a validated sham acupuncture device, this trial aims to isolate the specific therapeutic effects of electroacupuncture from non-specific effects, thereby enabling a comprehensive assessment of its efficacy, safety, and impact on pelvic floor function. However, a recognized limitation inherent to acupuncture trials, including this one, is the potential influence of non-specific effects, such as the placebo effect, patient expectations, and the therapeutic ritual. Although the sham acupuncture technique is designed to minimize placebo effects, the inability to blind the acupuncturists and the potential for patients to perceive differences in needle sensation between real and sham treatments remain essential potential sources of bias. To mitigate this risk, participants will receive interventions individually in separate rooms to prevent communication between them. Participants will be blinded to their group assignment to maintain objectivity.

Furthermore, concomitant pelvic floor muscle training is prohibited during the trial period to avoid confounding. If the trial demonstrates the superiority of electroacupuncture over sham treatment, the observed benefits may be attributed to mechanisms such as enhanced pelvic floor muscle tone, reduced muscle fatigue, and subsequent improvements in pelvic floor structure and continence function.

To quantitatively assess the success of blinding, we will use the Bang Blinding Index upon completion of the treatment period. Participants will be asked to guess their group assignment, and the results will be analyzed to determine the effectiveness of our blinding procedures. Successful blinding will help distinguish the specific effects of electroacupuncture from non-specific effects. Nevertheless, the inability to blind therapists and the potential for participants to discern treatment allocation remain inherent methodological limitations. These factors will be carefully considered when interpreting the trial results.

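### Training against unintentional unblinding leaves out the acupuncturists, who know the allocation and treat the participant, and no stated measure limits what they may convey

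*Protocol article*

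**What the plan says.** Section 2.6.3 (Blinding) sets out who is blind: "Participants, outcome assessors, and data analysts will remain blinded throughout the trial". It also states that "the acupuncturists administering the treatment cannot be blinded". To protect the blind it provides that "all research staff (except for the acupuncturists) will receive standardized training to prevent unintentional unblinding".

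The same section gives the acupuncturists their role. After baseline data collection, "the assigned acupuncturist will open the envelope to reveal the group-specific instructions", and "The same assigned acupuncturist will administer all treatment sessions for a given participant to ensure consistency". Section 2.4 (Interventions) fixes the number of contacts: three sessions a week of 30 minutes each, "totaling 18 sessions over 6 weeks".

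Section 2.3 describes the acupuncturists' own preparation as a one-week programme "covering acupoint localization, needle insertion depth, manipulation techniques, and safety protocols", followed by simulated sessions with an 85% agreement requirement on key parameters, for which technique items are given as examples.

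The Discussion names "the inability to blind the acupuncturists and the potential for patients to perceive differences in needle sensation between real and sham treatments" as remaining potential sources of bias.

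**The concern.** Training against unintentional unblinding serves two purposes: it helps blinded people stay blind, and it stops people who know the allocation from giving it away. The outcome assessors and data analysts need the first. The acupuncturists need the second, and the plan exempts them by name. That they cannot be blinded is no reason to leave them out, because what matters in their case is disclosure.

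The two arms also put the therapist in different situations. Under Section 2.4.1 the therapist seeks deqi and raises the current until a tremor is seen. Under Section 2.4.2 and Table 2 there is no manipulation, no deqi and no current. Without a common form of words, conversation about sensation and about whether the treatment is working can easily differ by arm.

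What is at stake is the reading of the EA-minus-sham difference. If encouragement or hints differ by arm, the difference includes an expectation effect carried by the therapist. The outcomes most open to this are those the participant reports herself: ICIQ-SF, diary incontinence episode frequency and self-rated benefit. The Discussion says the trial aims to separate specific from non-specific effects, and this route works against that aim.

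**Working it through.** The plan states no figure on this point, so the check sets each stated safeguard against the route in question: what an unblinded therapist conveys to a participant.

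**Inputs**

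- Knowledge of the arm: the acupuncturist opens the envelope (Section 2.6.3).
- Contact: the same acupuncturist at every session (Section 2.6.3). 3 sessions per week × 6 weeks = 18, which agrees with the total in Section 2.4.
- Scheduled session time: 18 × 30 min = 540 min = 9 h per participant. This is treatment time. The article does not say the therapist is present or talking throughout, so it is a ceiling on in-session contact, not a measure of it.

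**Safeguards, one by one**

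| Stated measure | Where | What it protects | Limits what the therapist conveys? |
|---|---|---|---|
| Training against unintentional unblinding | 2.6.3 | Staff other than the acupuncturists | No, acupuncturists are excepted |
| One-week operator training | 2.3 | Technique and safety | Not among the topics listed |
| 85% agreement in simulated sessions | 2.3 | Point location, depth, manipulation (given as examples) | Not among the examples |
| Separate rooms and appointment times | 2.6.3, Discussion | Contact between participants of different arms | No |
| Sham device of identical appearance, pads in both arms | 2.4.1, 2.4.2 | Visual concealment of the equipment | No |
| Blinded assessors and analysts | 2.6.3 | Assessment and analysis | No |
| Bang's blinding index | 2.6.3, Discussion | Measures blinding once treatment has ended | No, it detects a loss but does not prevent it |

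Each measure has a purpose, and none reaches this route.

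**Risk set against remedy.** The Discussion names two risks together: unblinded acupuncturists and perceptible differences in sensation. The mitigation it then describes is to treat women individually in separate rooms so that they do not talk to one another. That addresses a third route, communication between participants, and neither of the two just named. The later commitment to weigh these factors when interpreting the results is a disclosure, not a control.

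**Which outcomes.** Section 2.5.2 takes ICIQ-SF, diary episodes and perceived benefit from the participant. The primary outcome (Section 2.5.1) is a pad weighed after prescribed activities, with outcome assessors blinded. It is less exposed, and the article does not show that therapist talk would change it.

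**The case against.** The strongest reply is that the exception has an innocent reading. It closely follows the statement that the acupuncturists cannot be blinded, so the training may be meant only to keep blinded staff blind, for instance when a participant describes her sensations to an assessor. The commitment that participants stay blinded already implies non-disclosure. A journal article also condenses a longer protocol, and conduct rules may sit in an operating manual that is not shown. Section 2.4.2 says both interventions follow an earlier trial's methods and a sham-reporting guideline.

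Part of this stands. It cannot be concluded that no interaction rule exists anywhere, or that acupuncturists are free to disclose allocation. But the point rests on a stated rule about who is trained. Even on the innocent reading, the treating staff receive no stated instruction on non-disclosure or neutral interaction.

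Three stronger readings are tempting, and the document does not support them.

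- A reader might infer that the acupuncturists are the only staff who know the allocation. The independent statistician generates the sequence (Section 2.6.2), and rooms and appointments are arranged by group, so scheduling staff may know it too. What holds is that they are the only staff described who both know it and treat participants.
- A reader might infer that this is the main way participants could be unblinded. Real needles go 40–50 mm deep with deqi and current. Sham needles do not penetrate and no current is felt. Sensation is at least as plausible a route, the Discussion names both without ranking them, and a script would not remove it.
- A reader might try to put the bias in grams, or as a false-positive rate, by treating the 4.81 g sham change in Section 2.6.1 as response that cues could remove. That figure is a change from baseline. It may include regression to the mean, natural course and test variability, and the share that talk could remove would be pure assumption.

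It is also fair to the authors that they say the trial aims to isolate specific effects and that they disclose the limitation.

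**Conclusion.** The point holds in a limited form. The plan explicitly withholds training against unblinding from the staff who open the envelope and deliver all 18 sessions to a participant, and no other stated measure limits what they may convey. One important, controllable route to unblinding and unequal expectation is left open, alongside the acknowledged differences in sensation.

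The effect cannot be quantified from the document and no figure is offered. It would fall mainly on the participant-reported secondary outcomes. The conclusion assumes that the article's account of who is trained, and in what, reflects the trial as planned. If an operating manual already contains a neutral-interaction rule, what remains is to correct the sentence and cite that rule. This should be changed, but it does not invalidate the design.

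**What to change.** In Section 2.6.3, delete the exception so that the acupuncturists are included in the blinding training. In Section 2.3, add to their one-week programme:

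- a single neutral interaction script, identical in both arms, covering placement, questions about sensation, switching on the device, and replies to a participant who asks whether it is working;
- an instruction not to disclose allocation and not to discuss expected benefit;
- a check of adherence to the script in the simulated sessions already planned for the agreement assessment.

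The Discussion could then cite this measure beside the limitation it addresses, while still stating that differences in sensation remain.

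The cost is a change of wording, slightly longer training and more constrained conversation for the therapists. No extra staff or visits are needed, and the interventions, outcomes and sample size are unaffected.

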#### Statistical methods

2.6.4

Statistical analyses will be performed on the intention-to-treat (ITT) population and the per-protocol (PP) population. For the ITT analysis, missing data will be handled using multiple imputation by chained equations (MICE). All statistical analyses will be conducted using SPSS software (version 26.0; IBM Corp.). Results will be presented with 95% confidence intervals, and a two-sided *P* value of less than 0.05 will be considered statistically significant. Continuous variables normally distributed will be summarized as mean ± standard deviation, while those with a non-normal distribution will be summarized as median and interquartile range (IQR). Comparisons of continuous variables between the two groups will be performed using the independent samples *t*-test (for normal data) or the Mann–Whitney *U*-test (for non-normal data). Categorical data will be described as frequencies and percentages, and comparisons between groups will be made using the appropriate Chi-squared test or Fisher's exact test. For longitudinal analysis of outcomes measured over time, generalized estimating equations (GEE) or linear mixed-effects models will be employed to account for correlations within subjects and to examine time-by-group interaction effects. In secondary analyses, we will explore potential effect modification by menopausal status by including an interaction term in our statistical models. For the exploratory secondary outcomes, interpretation will focus on effect sizes and confidence intervals rather than unadjusted *P* values to avoid inflation of type I error due to multiple comparisons. No formal multiplicity adjustment will be applied to secondary endpoints.

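### Acupuncturist is neither balanced by the randomisation nor included in a stated analysis: a modest loss of precision, and a safeguard against bias that is only implied

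*Protocol article*

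**What the plan says.** All quotations are from the protocol article.

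- **Operators (2.3):** "Two licensed acupuncturists will perform all acupuncture procedures, each with at least five years of clinical experience". Both have a week of standardised training, and "Inter-operator consistency will be assessed through simulated treatment sessions, requiring at least 85% agreement on key parameters".
- **Exposure (2.4, 2.6.3):** each woman has three sessions a week, "totaling 18 sessions over 6 weeks", all from one acupuncturist: "The same assigned acupuncturist will administer all treatment sessions for a given participant to ensure consistency".
- **Order of events (2.6.3):** "After baseline data collection, the assigned acupuncturist will open the envelope to reveal the group-specific instructions". The same section places the two arms in separate rooms and at different times so that participants do not meet.
- **Randomisation (2.6.2):** a 1:1 sequence "employing a simple randomization procedure". No blocks or strata are mentioned.
- **Analysis (2.6.4):** "Comparisons of continuous variables between the two groups will be performed using the independent samples" t-test, or the Mann–Whitney test. The longitudinal models name within-subject correlation and time-by-group terms, and menopausal status is the only effect modifier. The Discussion names concomitant SUI treatments as the only covariates.

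The article does not say how a woman is given her acupuncturist, whether this may change after the envelope is opened, or that both acupuncturists treat both arms.

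**The concern.** Acupuncturist is a two-level factor that stays constant for each woman over the whole course. In the EA arm the acupuncturist elicits deqi and adjusts the current within its stated range. In both arms the acupuncturist supplies all the practitioner contact. If the two obtain different results, that difference is unexplained variation in the primary comparison. In a single trial it moves the estimate whenever one acupuncturist happens to treat more of one arm. With only two operators and 64 women, such splits are not rare.

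A second matter is the missing assignment rule. The arms have their own rooms and times, and the person who learns the allocation also treats. If operator came to be tied to arm, the operator difference would enter the treatment contrast systematically. With complete alignment no analysis could separate the two.

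**Working it through.** **Inputs.** From 2.6.1: means 8.59 g and 4.81 g (difference 3.78 g), SD 4.76 g, two-sided alpha 0.05, power 80%, dropout 20%. Assumed: each acupuncturist treats half the women, and the mean pad-test reduction differs between acupuncturists by g = 1 to 3 g, equally in both arms.

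**1. The plan's own figure.** n = 2 × (1.96 + 0.84)² × 4.76² / 3.78² = 15.68 × 22.66 / 14.29 = 24.86, so 25 per arm. Then 25 / 0.80 = 31.25, so 32 per arm and 64 in total. This agrees with the protocol.

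**2. How often imbalance occurs.** With arms of exactly 32 and 32 women per acupuncturist, the number k of one acupuncturist's women in the EA arm is hypergeometric (64, 32, 32).
- P(caseload differs by 6 or more between arms; 19 v 13 or worse) = 0.211
- P(caseload differs by 8 or more; 20 v 12 or worse) = 0.079

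Simple randomisation does not guarantee 32/32. Simulating independent coin tosses for 64 women, the between-arm difference in one acupuncturist's share has SD 0.127. It reaches 25 percentage points (the equivalent of 20 v 12) in about 6% of trials.

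**3. Size of the shift.** Shift = g × (20 − 12)/32 = 0.25 g.

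| Assumed difference g | Shift at 20 v 12 | Share of 3.78 g |
|---|---|---|
| 1 g | 0.25 g | 7% |
| 2 g | 0.50 g | 13% |
| 3 g | 0.75 g | 20% |

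A typical shift at 2 g is 0.127 × 2 = 0.25 g. The standard error of the contrast is 4.76 × √(2/32) = 1.19 g with 32 per arm, and 4.76 × √(2/25) = 1.35 g with 25 per arm.

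**4. Is it bias?** I simulated simple randomisation with acupuncturist fixed beforehand and 50 completers. The type I error of the unadjusted t-test was between 0.048 and 0.051 for g = 0 to 3 g. The mean estimate was 3.76 to 3.78 g against a true 3.78 g. The shifts average zero, and the test's standard error already covers them.

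**5. What balancing and adjustment gain.** Power with 50 completers, 200,000 simulated trials per cell. The last column starts from 64 women stratified 16 per arm and acupuncturist, with 14 lost at random.

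| g | Simple, unadjusted | Simple, with acupuncturist term | Stratified and blocked, with term |
|---|---|---|---|
| 0 g | 0.777 | 0.768 | 0.782 |
| 1 g | 0.772 | 0.768 | 0.781 |
| 2 g | 0.760 | 0.769 | 0.782 |
| 3 g | 0.737 | 0.767 | 0.782 |

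From the first column to the last, the gain is 2.2 points at 2 g and 4.5 points at 3 g, and 1 point or less at 0 to 1 g. A term added to a simple list gains nothing at 0 to 1 g.

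**The case against.** The strongest reply is that a factor fixed before allocation is a baseline covariate. Randomisation balances it in expectation, and the t-test allows for what chance leaves over. That stands, and it rules out calling the 20 v 12 shift bias.

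The assumed differences are also large: 2 g is 53% and 3 g is 79% of the whole planned effect. Both operators are experienced and jointly trained, and sham has no penetration, deqi or current for technical skill to act on. This stands as a reason to expect the lower end of the range. It does not remove the point, because the 85% agreement concerns technique in simulated sessions, not outcomes or practitioner contact.

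A model term may be left to an analysis plan that is not shown. That is fair for the term, but not for the list. Section 2.6.2 fixes simple randomisation, and balance by operator has to be built in before enrolment.

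A reader might infer from the separate rooms and times that each arm has its own acupuncturist, so that the EA–sham contrast is confounded with operator. The documents do not support this. The separation is described as keeping participants apart to protect blinding, no acupuncturist is tied to a room, and the envelope is opened by someone already assigned. If operator did follow arm for half the women, simulation at 2 g gives a bias of 1.0 g and a type I error of about 0.11. That shows why the rule should be written down; it is not an expected result.

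Nor could any analysis reliably tell whether the effect comes from one operator, with about 64/4 = 16 women per arm per acupuncturist.

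**Conclusion.** The point holds as an inexpensive improvement to the design. Acupuncturist is unbalanced by design and absent from the stated analyses. On the natural reading of 2.6.3 this leaves chance imbalance and some lost precision, with type I error near 0.05. The power at stake is negligible if the operators' results differ by 1 g or less, and about 2 to 4.5 points at 2 to 3 g. These sizes rest on an even caseload, 50 completers and an assumed operator difference common to both arms; none of these splits or differences is given in the protocol. Systematic bias is neither shown nor likely on the text. It remains possible only because the assignment rule is unstated.

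**What to change.** **In 2.6.2:** state that the acupuncturist is assigned before and independently of allocation, that this assignment is not changed after the envelope is opened, and that both acupuncturists treat both arms. Stratify the randomisation by acupuncturist, using randomly varying blocks whose sizes are concealed from the acupuncturists. Separate simple lists would not be enough: each woman would still be an independent coin toss, with the same chance imbalance as one list.

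**In 2.6.4:** replace the unadjusted primary comparison with a linear model containing arm and acupuncturist as a fixed two-level factor (two levels are too few for a random effect), using the acupuncturist assigned before allocation. Report the arm-by-acupuncturist counts and the EA–sham difference for each acupuncturist, descriptively only.

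**Cost:** two envelope series instead of one, one degree of freedom, one descriptive table, and slightly more predictable allocation from blocking, which matters because the acupuncturists are unblinded and open the envelopes. No extra participants, staff or visits are needed.
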